### Routine visits in intervention clusters

Upon completion of enrollment and the baseline survey, enrolled mothers in areas selected for the intervention will be visited by the CDAs. Routine visits will focus on:

1. *Health and Nutrition Monitoring*

Each visit in intervention clusters will start with a review of the child’s health status and an update since the previous visit. CDAs will have previously reviewed the child’s under-5 card and will have reminders on which children are behind with their vaccinations and check-ups. At each visit, the CDA will review the child health card with the caregiver, and inform and refer to the clinic if the child has missed an immunization, health check-up or a routine treatment such as deworming or vitamin A supplementation. The CDA will also remind the mother of upcoming routine health check-ups for the child. The CDA will measure the child’s MUAC[[41](#_ENREF_41)] every month and communicate the result to the mother. If the result shows signs of moderate to severe acute malnutrition or a poor growth pattern, the CDA will refer the child to the clinic. Following WHO/UNICEF guidelines [[42](#_ENREF_42)], we will classify all children as severely malnourished if their MUAC is less than 115 millimeters (11.5 centimeters). In case of malnutrition, the CDA may also work with the mother to suggest an affordable, local, and nutritionally appropriate diet for the child following Ministry guidelines and the ones of the Zambia National Food and Nutrition Commission. The CDA will also ask about presence of acute infectious diseases such as fever, diarrhea, cough or difficulty breathing, worms and refer to the clinic and to a community-based health worker such as a CHA or CHW if any of these are present. The routine visits for health and nutrition monitoring will last for 12 months.

1. *Cognitive Stimulation/Parenting Intervention facilitation and check-up.*

CDAs will also ask local headman for their support in finding volunteers for the community-based early childhood learning groups. Volunteers will be trained to lead the community-based parenting intervention (for being the “head mother”) by the CDA, who will supervise and mentor the volunteers. This training will occur on a regular basis during the CDAs biweekly visits to the local community. Before the beginning of the study, head mothers may also receive half a day of formal training. Volunteer mothers will receive the training material and the informational material that will be the core of each meeting by the CDAs. The “head mothers” will be responsible for organizing a meeting at least once a week with all of the other interested mothers, and especially caregivers of children who are part of the study. During each session the mother will lead a discussion on the information material representing the topic of that session, and will be in charge of stimulating a discussion. There will also be homemade toys created with local material or other sessions where specific songs, rhymes, or games will be taught. The CDA will attend the parenting group on a regular basis, but not each week, to monitor the quality of the information that is given. Every time the CDA visits a community, she will also visit the head mother to refresh her training for the following lessons, to troubleshoot any day-to-day problems, to make sure that the meetings are ongoing and to answer to any questions. During routine visits with the caregivers in the study, the CDA will also review the material that was discussed at that week, and give the caregivers the opportunity to ask questions. The parenting program is set to last for 9 months. We anticipate that it will start around month 3 of the intervention.

An example of the early childhood development curriculum is attached in Appendix B. We have 25 weekly classes that are focused on introducing the course, cognitive development, maternal health and wellbeing, socio-emotional development, communication, gross motor development, fine motor development, rights and protection, nutrition, hygiene and child health. Over the course of the ECD curriculum, both theory and practical applications of the health and development messages will be taught. Some practical applications include toy making and learning new songs.

**Endline Assessment**

Twelve months after enrollment all children will be visited for a final follow-up interview and assessment. This assessment will be done by a separately trained team of child assessors, and will include the questions asked at baseline as well as an assessment of child development using a standardized test, the INTERGROWTH 21^st^ century assessment tools.

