## Specific objectives

**Specific objective #1:** To conduct a cluster-randomized controlled trial to determine whether a community-based package of interventions targeted at early childhood development (ECD) and delivered by community development agents (CDAs) can reduce stunting and improve cognitive and motor development by two years of age.

The study will have two primary outcomes:

1. **Prevalence of stunting (height-for-age z-score (HAZ) < -2) at age 2.**
2. **Cognitive and motor development by age 2 years as measured with a standardized test developed as part of the multinational INTERGROWTH-21^st^ study** [[13](#_ENREF_13)]. The assessment tool combines elements of four existing testing instruments (Bayley Scales of Infant Development (BSID), the Rapid Neurodevelopment Assessment (RNDA), the Malawi Development Assessment Tool and the Griffith’s Scales) and simultaneously assesses cognition, language, motor skills and behavior.

**Specific objective #2:** To determine whether the intervention improves effective access to child health services. This will be measured by the following secondary outcomes:

- Vaccination rates
- Vitamin A supplementation
- Utilization of routine child health check-up services

**Specific objective #3:** To determine whether the intervention alters caregiver interactions with children. We will use the *Home Observation for Measurement of the Environment* (HOME) inventory [[14](#_ENREF_14)]. This will be measured by the following secondary outcomes:

- Availability of books, toys and other reading materials at home
- Time spent by caregivers reading to the child
- Time spent by caregivers playing with the child

**Specific objective #4:** To determine whether there are secondary benefits of mother/caregiver-led-support groups in terms of maternal mental health. This will be measured by the following secondary outcomes:

- Maternal depression, captured with the SRQ-20 questionnaire, a test validated internationally including in neighboring Malawi[[15](#_ENREF_15)]

**Specific objective #5:** To determine the types and quality of nutrition services currently provided in the five health centers and referral feeding centers. This will be collected via a structured KII with nutritionist or clinical care specialists at the national, provincial and district levels. Questions will focus on:

- Current policies and guidelines relating to child health and nutrition

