**Specific objective #6:** To determine the relationship between the 5 selected health facilities’ quality (measured and perceived) and parents’ use of services for malnourished children. Both perceived and parents’ use of services will be collected via questions collected on baseline data regarding satisfaction to health facility services. Facility quality will be determined by a structured KII with health facility staff. Questions for health facility staff will focus on:

- Health worker knowledge on treatment of malnourished children
- Health facility screening procedures
- Quality of nutrition services
- Audit of clinic resources

**Specific Objective #7:** To assess the usual diet of 6-12 month old infants. We will use a form that utilizes the 24-hour recall method to measure quantities and types of foods consumed by the child in the past 24-hours as reported by the mother.

- Measure by 24-hour recall, time and food or beverage consumed
- Aid of measuring cups, food pictures and diagrams

**Specific Objective #8:** Describe and document the perceptions of mothers on mother groups, as well as any behavioral changes in parenting or in mother support networks resulting from participation in mother groups.

This will be done through focus group discussions and analyzed with qualitative analysis methods.

**Specific Objective #9: A**ssess parenting behavior prior to the start of the mothers’ group extension, in April 2016.

We will visit all study households (intervention and control) in April 2016 and collect information on a short set of parenting behaviors. We have attached the instrument we will use. The parenting behaviors we will assess are the same as those assessed during previous household surveys for this study. We will also obtain a new informed consent form from all study households at this visit.

**Specific Objective #10:** Assess the impact on parenting practices and primary outcomes after extending the mother groups component for an additional period of time (7 months).

While the assessment of cognitive development at less than 2 years of age is very difficult and is and not-precise, the assessment closer to 3 years-old can be more reliable. We will continue the mothers’ groups component of the study (parenting) for 7 additional months, then re-assess the cognitive development of the children as well as parenting practices.

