## Eligibility Criteria

Inclusion

- Children aged 6-12 months in the catchment areas of the five selected health facilities in Southern Province will be eligible to participate
- Child’s primary caregiver must be 15 years or older
- Child’s primary caregiver must be a female (because the participants in the women’s group may feel uncomfortable discussing certain issues if a man is present)
- Health workers working at the five health centers where the study is taking place
- District and provincial level nutritionists or clinical care specialists

Exclusion

- Caregivers who are unwilling to provide informed consent
- Families that plan to move from their health center catchment zone during the twelve month period of the study
- Health workers, nutritionists, or clinical care specialists who refuse to provide informed consent

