# Time Frame

| Development of intervention materials and BU IRB/Zambian ethics committee approvals | Sept 2013 – April 2014 |
| --- | --- |
| Surveyor and CDA recruitment and training | April 2014 |
| Pre-testing data collection instruments, enrollment and baseline survey | May 2014 |
| Intervention rollout | September 2014 |
| Endline evaluation | October 2015 |
| Data analysis | November 2015 |
| Year 1 report and data dissemination | December 2015 |
| Parenting assessment | April 2016 |
| Mothers group extension | April 2016 |
| Year 2 (follow-up) evaluation | November 2016 |

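### The protocol gives two incompatible endline schedules (ages 18–24 months or about 23–29 months), and neither fits both primary outcome definitions, stunting at age 2 and development by age 2

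*Protocol*

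**What the plan says.** Specific objective #1 sets the two primary outcomes. The first is "Prevalence of stunting (height-for-age z-score (HAZ) < -2) at age 2". The second is "Cognitive and motor development by age 2 years as measured with a standardized test". So stunting is tied to the age itself, and development only to an upper limit on age.

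The Eligibility Criteria section admits "Children aged 6-12 months in the catchment areas of the five selected health facilities". It excludes families who plan to leave the catchment zone within a study period that it gives as twelve months.

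The Endline Assessment section fixes the interval: "Twelve months after enrollment all children will be visited for a final follow-up interview and assessment".

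The Time Frame gives calendar dates: enrolment and baseline survey in May 2014, intervention rollout in September 2014, and "Endline evaluation | October 2015". The analysis text for Objective 9 also dates the last assessment to October 2015, so the table entry is not a stray one.

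Objective 10 justifies a later reassessment by saying that "the assessment of cognitive development at less than 2 years of age is very difficult". This implies that the first developmental assessment falls before the second birthday.

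The Data analysis section repeats both primary outcomes with no age attached. No section gives an age window, and none provides for a visit at the second birthday.

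**The concern.** The time of measurement is part of the definition of a primary outcome. Here the objectives, the endline rule and the timetable each imply a time, and they cannot all be right.

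Two things are at stake. The first is interpretation: stunting prevalence and raw development scores depend on age, so a result reported as applying at or by age 2 would be mislabelled for most children on at least one outcome, whichever schedule was followed. The second is consistency elsewhere. A 17-month follow-up does not match the twelve months in the exclusion criterion, under which a family planning to leave in months 13–17 passes screening. Nor does it match the statement in Objective 10 that children were under 2 when first tested.

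**Working it through.** **Inputs.** Age at enrolment 6–12 months (Eligibility Criteria); interval 12 months from enrolment (Endline Assessment); enrolment and baseline May 2014, rollout September 2014, endline October 2015 (Time Frame).

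**Formula.** Age at endline = age at enrolment + interval from enrolment to endline.

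**1. The text rule.** 6 + 12 = 18 and 12 + 12 = 24, so ages are 18–24 months.

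**2. The timetable.** May 2014 to May 2015 is 12 months, and on to October 2015 is 5 more, so the interval is 17 months. 6 + 17 = 23 and 12 + 17 = 29, so ages are about 23–29 months. The stated 12 months is not reproduced.

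**3. A reading that might reconcile them.** Counted from rollout, September 2014 to October 2015 is 13 months, close to 12. The 4 months between baseline and rollout (May to September 2014) account for most of the 5-month difference. If children were 6–12 months old at rollout, endline ages would be 6 + 13 = 19 to 12 + 13 = 25 months. However, the Endline Assessment section counts from enrolment, and the timetable puts enrolment in May.

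**4. How many children are near age 2.** The protocol gives no age distribution. Assuming ages spread evenly over the 6-month band:

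| Schedule | Interval (months) | Age at endline (months) | Under 24 months | Within 1 month of 24 |
| --- | --- | --- | --- | --- |
| Text rule, from enrolment | 12 | 18–24 | 6/6 = 100% | 1/6 = 17% |
| Timetable, from May 2014 | 17 | 23–29 | 1/6 = 17% | 2/6 = 33% |
| From rollout, if aged 6–12 months then | 13 | 19–25 | 5/6 = 83% | 2/6 = 33% |

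**5. Against the outcome definitions.** The text rule satisfies the development outcome, since every child is assessed by age 2, but almost no child has reached age 2 for stunting. The timetable brings more children close to age 2 for stunting, but about 1 − 17% = 83% are past the limit set for development. It also contradicts Objective 10, because only about 17% would still be under 2.

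**6. Does either schedule cut the programme short?** In the text, home visits start once enrolment and baseline are complete and run 12 months. The groups start around month 3, and "The parenting program is set to last for 9 months", so they end at 3 + 9 = 12 months, when the endline falls due. In the timetable, the endline is 13 months after rollout. Each schedule, taken alone, leaves room for full delivery.

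**The case against.** The strongest reply is that this is loose wording. Enrolment was probably used for the start of the intervention, and 13 months from rollout is near enough to 12. The document was revised after Year 1 and itself places the assessment in October 2015, so the field team evidently worked to one date. The development outcome says by age 2, which ages of 18–24 months satisfy. All children in both arms follow the same schedule, and height-for-age is age-standardised, so the comparison is not biased. The remark on imprecise testing before age 2 is already acted on: it is the stated reason for the reassessment nearer age 3.

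Most of this stands, and it limits the point. It does not remove it. The words still say enrolment, the timetable still puts enrolment in May 2014, and no reading makes the outcome definitions, the interval and Objective 10 agree.

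A reader might infer more: that the endline precedes completion of the programme and so favours a false null. Twelve months after May 2014 is May 2015, 8 months after rollout, which would mean 8 of 12 months of visits and about 5–6 of 9 months of groups. Scaling the planned 0.5 SD effect by 5.5/9 gives 0.31 SD, at which power would be under 60%. The documents do not support this. The shortfall appears only when the interval from the text is combined with the rollout date from the timetable; step 6 shows that neither schedule produces it. The document's own October 2015 date rules out a May 2015 endline, and the scaling assumes a linear dose-response that the protocol nowhere states.

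**Conclusion.** The contradiction is real and should be corrected. The interval from enrolment to endline is 12 months in one place and 17 in another, and age at endline is 18–24 or about 23–29 months. The time point stated for stunting fails on the first schedule, and that stated for development fails for most children on the second.

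The interval of 17 months rests on the calendar months given. The range of 23–29 months further assumes that every child was 6–12 months old in May 2014, and the percentages assume evenly spread enrolment ages. The conflict itself needs neither of these last two assumptions.

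The consequence is a misstated age at measurement, and hence a misstated claim about what the primary outcomes show. The discrepancy does not by itself bias the comparison between arms, and the sample-size inputs are unaffected.

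**What to change.** Reconcile Specific objectives #1 and #10, the exclusion criterion, the Endline Assessment section and the Time Frame to one anchor consistent with the October 2015 endline: for example, about 12–13 months after the September 2014 rollout, which is about 17 months after baseline.

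Restate both primary outcomes as measured at endline, and give the actual interval and the observed age range in place of at or by age 2. Do not write in 23–29 months as fact: use the recorded ages, because that range is inferred. Correct the Objective 10 remark to the ages observed, and state what follow-up period the twelve months in the exclusion criterion was meant to cover.

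Include the child's age at assessment as a covariate in the development-score model. Ages span at least 6 months on any reading, and the covariates named in the Data analysis section do not include age.

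The cost is wording plus one covariate. Age at assessment can be derived from data already collected, since height-for-age cannot be computed without it. No new visit or measurement is needed.

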### 3.1.2 Internal validity

Power calculations indicate that the selected number of health zones will be sufficient to detect the expected impact on our primary outcomes. After randomization, the soundness of the randomization as a procedure to control for confounding will be checked by comparing variables obtained through the baseline survey and through community level data. Examples of baseline variables that will be compared are maternal age, education and occupation; child age and gender; birth weight of the child; duration of breastfeeding length; and initial vaccination status. We will also include community level baseline variables such as distance to health center and District Medical Office, road access and presence of community health workers. Although blinding of treatment will not be possible due to the very nature of the intervention, we do not expect Hawthorne effects to be significant in this case due to the length of the program. We also do not foresee important concerns due to differential attrition in the two arms because of the long-standing relationship of ZCAHRD in all of these communities (both the control and intervention) established through the previous ZamCAT study.

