# Data analysis

We will use the following primary outcomes:

1. Proportion of children with stunting (height-for-age Z-score less than 2 standard deviations below the mean);
2. Child development scores using the INTERGROWTH tool;

Other outcomes of interest include:

1. Proportion of children receiving all age-appropriate vaccines
2. Proportion of children receiving vitamin A supplementation;
3. Number of well-baby visits attended;
4. HOME score;
5. Average time spent reading with the child;
6. Average time spent playing with the child;
7. Proportion of women scoring as depressed, based on the SRQ-20.

We will investigate the relative risk associated with random group assignment as a fixed covariate predicting each outcome using generalized estimating equations (GEE) models that take into account the clustering by health facility. We will use an exchangeable correlation structure in the model.

We will compare baseline characteristics between the two groups that may be related to the outcome, but we expect randomization to have created reasonably balanced groups. Categorical variables will be compared between groups using the chi-square test or Fisher’s exact test if cell sizes are small, continuous variables using t-tests if normally distributed or non-parametric Wilcoxon rank sum tests, if non-normal. We will adjust for confounders as appropriate.

Potential confounders include: maternal education, paternal education, socio-economic status, baseline nutritional status, and presence of food insecurity. The process of randomization should help to balance confounders across the two study arms. Crude and adjusted risk ratios will be presented with 95% confidence intervals in appropriate tables.

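### The protocol addresses blinding of treatment only and provides no masking of the assessors who score the developmental primary outcome, at endline or at year two

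*Protocol*

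**What the plan says.** Section 3.1.2 (Internal validity) contains the only mention of blinding: "Although blinding of treatment will not be possible due to the very nature of the intervention, we do not expect Hawthorne effects to be significant". It goes on to discount differential attrition. It does not discuss bias in how outcomes are measured.

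The Endline Assessment paragraph sets the visit: "Twelve months after enrollment all children will be visited for a final follow-up interview and assessment". On who does it: "This assessment will be done by a separately trained team of child assessors". On its content, the visit "will include the questions asked at baseline as well as an assessment of child development using a standardized test". No order is given for interview and test, and nothing is said about what the assessors know of allocation.

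The two primary outcomes in the Data analysis section are "Proportion of children with stunting (height-for-age Z-score less than 2 standard deviations below the mean)" and "Child development scores using the INTERGROWTH tool". For year two, the second becomes a BSID-III score. The paragraph on extending the mother groups does not say who administers it.

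**The concern.** The reason given for not blinding applies to those who receive or deliver the intervention. It does not apply to a separate team that only tests and measures the child. Separate training is not masking: a well-trained assessor who knows which zones had CDAs and mother groups can still score in their favour without intending to.

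The endline visit makes such knowledge likely. The repeated baseline questions cover books and toys in the home, time spent reading and playing, and whether other programmes for young children operate locally. The intervention acts on the same things: "There will also be homemade toys created with local material or other sessions where specific songs, rhymes, or games will be taught". If the interview comes first, the assessor may learn the arm before scoring the child.

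At stake is a co-primary outcome. A systematic difference in scoring adds directly to the estimated effect. Neither more children nor the planned generalized estimating equations remove it. It has to be prevented in the conduct of the visit, so it belongs in the protocol, and a later analysis plan cannot supply it.

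**Working it through.** **Text, side by side**

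| Question | Endline | Year two |
|---|---|---|
| Who assesses? | A separate, trained team | Not stated |
| Are assessors told allocation? | Not stated | Not stated |
| Order of test and interview? | Not stated | Not stated |
| Content that can reveal the arm? | Yes: toys, reading, play, local programmes | Yes: parenting practices are re-assessed |
| Are both arms assessed? | Yes | Unclear: the extension paragraph speaks of children in the intervention component |

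**Design figure reproduced.** Inputs from Sample Size Calculations: effect 0.5 SD, power 0.9, 20 children per zone, intraclass correlation 0.1, 250 per arm. A two-sided 5% level is assumed; the protocol does not state one.

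- Design effect: 1 + (20 − 1) × 0.1 = 2.9, as stated.
- Individually randomised size: 2 × (1.960 + 1.282)² / 0.5² = 84.1, so 85 per arm.
- With clustering: 85 × 2.9 = 246.5, against 250 stated.
- Power with 250 per arm: 0.907, against 0.9 stated.

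The stated size therefore reproduces and is not in dispute. Masking would change none of these figures.

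**Illustration of a scoring shift.** The documents give no figure for observer bias, so the shift *b* is an assumption, shown over a range.

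- Standard error of the arm difference: √(2 × 2.9 / 250) = 0.152 SD.
- With no true effect, the chance of a significant result is 1 − Φ(1.96 − b/SE) + Φ(−1.96 − b/SE).

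| Assumed shift (SD) | b/SE | Two-sided error | Share of 0.5 SD target | Share of 0.3 SD year-two target |
|---|---|---|---|---|
| 0 | 0 | 5% | 0% | 0% |
| 0.05 | 0.33 | 6% | 10% | 17% |
| 0.10 | 0.66 | 10% | 20% | 33% |
| 0.15 | 0.98 | 17% | 30% | 50% |
| 0.20 | 1.31 | 26% | 40% | 67% |

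With 500 children in 30 zones, the average is 16.7 per zone rather than 20. The design effect is then 2.567 and the standard error 0.143 SD. Shifts of 0.10, 0.15 and 0.20 SD then give 11%, 18% and 29%, which does not alter the conclusion.

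**The case against.** The strongest reply is that the protocol never says the assessors will know the arm, and that it already has partial safeguards.

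- The endline team is separate from the CDAs who deliver the intervention.
- The study ID carries a facility code and a running number, not the arm, and every facility contains zones of both arms.
- The developmental test is standardised.
- The interview is not placed before the test; the order is simply left open.

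These points stand, and they make masking easier to add. They do not amount to masking, because nothing withholds the allocation or protects the score from what the interview discloses.

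Three stronger readings are tempting, and the documents support none of them.

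- A reader might infer that masking was considered and rejected outright. The sentence in section 3.1.2 concerns treatment and participants' reactions; on assessors the protocol is silent.
- A reader might infer that masking would be free and complete. The documents say nothing on its cost or feasibility. Home visits, homemade toys and caregivers' remarks can reveal the arm, and one facility is described as isolated, so spreading assessors across zones may add travel.
- A reader might treat both primaries as equally exposed. Stunting comes from a measured height and a fixed cut-off. It is not immune, but it leaves less room for judgement than a test score.

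**Conclusion.** The concern holds in a limited form. The protocol covers blinding of treatment only and provides no masking for the endline assessors or the year-two BSID-III assessors. The developmental co-primary depends on the observer, and the visit includes questions that can disclose the arm. It should be corrected, but it is not evidence that biased scoring occurred.

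The error rates of about 10%, 17% and 26% rest on assumed shifts of 0.10, 0.15 and 0.20 SD, a two-sided 5% level, a normal approximation and the protocol's design effect of 2.9. They show how sensitive the result is and do not estimate the bias. They apply to the developmental score and were not worked out for the binary stunting outcome.

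For year two the point further assumes that control children are assessed as well. The power statement for the BSID-III suggests a comparison, but the extension paragraph leaves this unclear.

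**What to change.** State in the protocol, for both endline and year two, that:

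1. child assessors are not told zone allocation;
2. the developmental test and anthropometry are completed and recorded before the caregiver questionnaire begins;
3. each assessor works in both intervention and control zones, within a facility where travel allows;
4. CDAs take no part in the year-two outcome assessment, in line with the separate team already planned for endline;
5. the assessor records any unmasking, with its timing relative to scoring.

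The current text already refers to first-year results. If the endline visits are complete, the protocol should instead document what those assessors knew and in what order they worked. The year-two evaluation, scheduled for November 2016, is where the procedures can still be set in advance. The extension paragraph should also say who the year-two assessors are and whether control children are assessed.

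The cost is scheduling and training for a team that already exists at endline, possibly with some extra travel. Sample size and analysis do not change. Masking will be incomplete, but testing the child first protects the score from anything disclosed in the interview.
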